# A Digital System (YouXin) to Facilitate Self-Management by People With Psychosis in China: Protocol for a Nonrandomized Validity and Feasibility Study With a Mixed Methods Design

**DOI:** 10.2196/45170

**Published:** 2023-09-12

**Keywords:** psychosis, self-management, digital, smartphone app, eHealth, mHealth, China

## Abstract

**Background:**

Psychosis is one of the most disabling mental health conditions and causes significant personal, social, and economic burden. Accurate and timely symptom monitoring is critical to offering prompt and time-sensitive clinical services. Digital health is a promising solution for the barriers encountered by conventional symptom monitoring approaches, including accessibility, the ecological validity of assessments, and recall bias. However, to date, there has been no digital health technology developed to support self-management for people with psychosis in China.

**Objective:**

We report the study protocol to evaluate the validity, feasibility, acceptability, usability, and safety of a symptom self-monitoring smartphone app (YouXin; Chinese name 佑心) for people with psychosis in China.

**Methods:**

This is a nonrandomized validity and feasibility study with a mixed methods design. The study was approved by the University of Manchester and Beijing Anding Hospital Research Ethics Committee. YouXin is a smartphone app designed to facilitate symptom self-monitoring for people with psychosis. YouXin has 2 core functions: active monitoring of symptoms (ie, smartphone survey) and passive monitoring of behavioral activity (ie, passive data collection via embedded smartphone sensors). The development process of YouXin utilized a systematic coproduction approach. A series of coproduction consultation meetings was conducted by the principal researcher with service users and clinicians to maximize the usability and acceptability of the app for end users. Participants with psychosis aged 16 years to 65 years were recruited from Beijing Anding Hospital, Beijing, China. All participants were invited to use the YouXin app to self-monitor symptoms for 4 weeks. At the end of the 4-week follow-up, we invited participants to take part in a qualitative interview to explore the acceptability of the app and trial procedures postintervention.

**Results:**

Recruitment to the study was initiated in August 2022. Of the 47 participants who were approached for the study from August 2022 to October 2022, 41 participants agreed to take part in the study. We excluded 1 of the 41 participants for not meeting the inclusion criteria, leaving a total of 40 participants who began the study. As of December 2022, 40 participants had completed the study, and the recruitment was complete.

**Conclusions:**

This study is the first to develop and test a symptom self-monitoring app specifically designed for people with psychosis in China. If the study shows the feasibility of YouXin, a potential future direction is to integrate the app into clinical workflows to facilitate digital mental health care for people with psychosis in China. This study will inform improvements to the app, trial procedures, and implementation strategies with this population. Moreover, the findings of this trial could lead to optimization of digital health technologies designed for people with psychosis in China.

**International Registered Report Identifier (IRRID):**

DERR1-10.2196/45170

## Introduction

### Background

Psychosis is one of the most disabling mental health conditions and causes significant personal, social, and economic burden [1], which increases the risk of physical health problems and reduces life expectancy by around 20 years [2]. Within 5 years after the first episode, 80% of people with psychosis will have at least one relapse [3]. The prevalence of schizophrenia in China is the highest in the world [4]. A recent Chinese national survey showed that the lifetime prevalence rate of schizophrenia and other psychotic disorders was 0.7% [5], and schizophrenia accounted for 13.7% of all mental and substance disorder disability-adjusted life years in 2019 [6].

Accurate and timely symptom monitoring is arguably one of the essential components of quality clinical services. Conventional symptom monitoring approaches in mental health services face several practical and methodological challenges. First, conventional methods rely on clinical interviews or comprehensive assessment batteries, which can be carried out only by trained professionals and require service users to attend an in-person meeting with their health provider. However, a lack of resources means that access to in-person services is limited; the wait times between referral and assessment can range from 4 weeks to 6 months or longer [7]. Meanwhile, organizational barriers (eg, financial availability, transportation) and attitudinal barriers (eg, stigma, reluctance to seek help) prevent people with mental health problems from attending appointments regularly [8]. Moreover, accessing in-person services has been further hindered by the COVID-19 pandemic, since clinic visits have been restricted to mitigate virus transmission [9,10].

Second, the conventional approach to assessing symptoms lacks ecological validity; current methods for assessing service users’ difficulties, broadly speaking, capture cross-sectional information rather than continuous information over a certain period of time [11,12]. Clinical visits tend to be scheduled mostly, at best, monthly, which means health care providers only get a snapshot of service users' conditions every 2 weeks to 6 weeks. However, clinically meaningful symptom fluctuation, such as mood or hallucinations, may occur on a daily basis [13], which conventional methods struggle to capture.

Third, recall bias has long been identified as a limitation of conventional clinical assessment methods [11,14]. Service users, especially people with severe mental health problems for which cognitive impairments are common [15], may have trouble accurately recalling their thoughts, feelings, and behaviors over a preceding period of time, making recall experiences at a granular level challenging [16]. Therefore, to optimize the quality of assessment and capture symptom fluctuation in a real-time, real-world granular manner, more ecologically valid assessment methods are needed.

The aforementioned barriers affect countries worldwide [14], even high-income countries with sophisticated mental health service systems (eg, the United Kingdom and the United States) [17,18], and China has been no exception to these challenges.

### Mental Health Services in China

China has invested substantial resources to reform its mental health system to improve the accessibility and quality of mental health services in the past 15 years; however, the effort has only been partially successful, and the mental health treatment gap remains significant [19,20]. The estimated shortage of mental health professionals in China was 40,000 relative to the population need [21]. According to the WHO Global Health Observatory, as of 2015, there were only 2.20 psychiatrists, 5.42 mental health nurses, and 0.07 mental health hospitals per 100,000 population in China [22]. In contrast, in the United States, there are 10.54 psychiatrists, 4.28 mental health nurses, and 0.19 mental hospitals per 100,000 population [22]. Moreover, since the Chinese health care system is designed as hospital-centered care [23], most well-trained mental health care professionals (ie, psychiatrists, mental health nurses, and psychologists) are concentrated in psychiatric hospitals located in urban areas, which makes it difficult for people in rural or remote communities to access care [24,25].

In China, mental health services are primarily delivered through psychiatric hospitals [26-28]. Compared with other settings (ie, general hospitals and community-based settings), tertiary psychiatric hospitals are best placed to provide quality mental health services, which results in service users overwhelmingly concentrated in tertiary psychiatric hospitals causing long wait times and reduced service quality [26].

### The Role of Digital Health

Digital health is a promising solution to address both the barriers encountered by the conventional symptom monitoring approach [14] and China’s health care system that has a shortage of mental health care resources [29,30]. The ubiquitous accessibility of digital technologies (eg, smartphones) provides unprecedented potential to scale-up service provision. Smartphone ownership rates in China have reached 96% [31]. Previous studies showed that smartphone ownership by people with psychosis was comparable with that of the general population [32]. More specifically, the internet access rate reached 90.9% of people with a diagnosis of schizophrenia in Hong Kong [33], and people with mental health problems in China in general were willing to accept mobile health interventions and considered them helpful [34]. Integrating digital health technologies (DHTs) into clinical workflows provides the potential to augment evidence-based care, support shared decision-making, and increase continuity of care [35]. These potential benefits are true for all countries worldwide and arguably even more so for countries with less sophisticated mental health care systems such as China. We conducted a systematic review on digital mental health in China and found that DHTs were generally feasible and acceptable among people with mental health problems, including people diagnosed with schizophrenia [29].

Among different types of DHTs, smartphones are the most advantageous tool for symptom monitoring given their ability to generate a plethora of data through active and passive monitoring methods [14]. Active monitoring is typically defined as the user self-reporting data (eg, psychological, behavioral, physiological) by ecological momentary assessment or other ambulatory assessment methods [12]. Passive monitoring refers to using the smartphone and its embedded sensors or a wearable device to measure the user’s behavior pattern (eg, app usage, activity log) or contextual information (eg, location) via passive user data collection [36]. By combining active and passive monitoring, smartphone-based monitoring has the potential to provide a more dynamic, personal, and valid representation of a person’s emotional and behavioral state [16,37]. Additionally, studies have shown that active self-monitoring of symptoms can reduce positive psychotic symptoms in people with recent-onset psychosis [38].

Smartphone-based symptom monitoring for people with psychosis has proved to be feasible in the Western context [39]; however, only 1 study conducted in non-Western, low and middle-income countries tested a digital platform with a symptom monitoring element [40]. To date, no smartphone-based symptom monitoring tool has been developed and evaluated for people with psychosis in China [29].

### Study Objectives

The aims of this study are to evaluate the validity, feasibility, acceptability, and safety of a symptom self-monitoring smartphone app (YouXin) for people with psychosis in China.

## Methods

### Ethical Considerations

The study was approved by the University of Manchester (Ref: 2022-13262-24297) and Beijing Anding Hospital (Ref: [2021] Research No.58 ) Research Ethics Committee. The study was conducted in full conformance with all relevant legal requirements and the principles of the Declaration of Helsinki, Good Clinical Practice, and the UK Policy Framework for Health and Social Care Research 2017. Potential participants were given a participant information sheet to read. The detailed informed consent procedure is described in the Recruitment section. Participants were informed that they are free to withdraw from the study at any time and for any reason. Withdrawal from the study did not impact participants' access to standard care at Beijing Anding Hospital. The delivery of the intervention did not affect any form of clinical care participants received, and they continued to be actively supported by the hospital during their participation in the study. Study data are anonymous and were managed according to the data management plan described in the Data Management section. Participants were given a ¥100 (US $13.76) gift voucher for each completed assessment. For participants who took part in the interview, at the end, they were given a ¥100 (US $13.76) gift voucher as a thank you for their time and to cover any costs incurred as a result of their participation. This information was included in the participant information sheet and was provided to participants before they entered the study.

### Study Setting

The study took place at Beijing Anding Hospital of Capital Medical University, which is one of the largest tertiary psychiatric hospitals in the Beijing metropolitan area. The hospital has 800 beds, an average 5000 inpatient admissions per year, and over 1200 daily outpatient visits.

### Study Design

The study uses a mixed methods design consisting of a nonrandomized feasibility study and a nested qualitative acceptability study. The study was designed according to the Consolidated Standards of Reporting Trials (CONSORT) statement extension for pilot and feasibility studies [41]. We recruited 40 people with psychosis at a tertiary-level psychiatric hospital in Beijing, China. This number is in line with other feasibility studies and sufficient to report on response rates, follow-up rates, safety information, and attrition, as well as the clinical characteristics of our study population at the beginning of the study and at follow-up [42]. Formal power calculations for treatment effects are not appropriate for a study primarily aimed at establishing feasibility. This sample size means a monthly recruitment target of 10 participants. Moreover, monitoring the recruitment target is part of the feasibility outcomes.

### Eligibility Criteria

Eligibility criteria were deliberately inclusive to fully assess feasibility and validity of the app and to reach generalizable conclusions for a wide range of service users with psychosis. Due to the limited resources, the research team could not provide devices to participants who did not own a smartphone. However, according to a recent survey study in China, 83.2% of service users and family members reported owning and frequent use of mobile devices [34]. Participant inclusion and exclusion criteria are presented in Textbox 1.

Inclusion and exclusion criteria.
**Inclusion criteria:**
Diagnosed with schizophrenia spectrum according to DSM-5 (F20-F29) or met the criteria for being at clinically high risk for developing psychosis according to the Structured Interview for Prodromal Syndromes (SIPS)Aged 16 years to 65 yearsReceiving care from Beijing Anding Hospital and will continue to be actively supported by the hospital over the next 5 weeks (ie, the duration of the project’s participant enrollment period)Own and able to use a smartphone

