#### Validity

The validity of active monitoring items will be assessed against relevant clinical assessments (ie, PANSS and CDSS) using Spearman correlation. An exploratory analysis will also be conducted to understand the association between mobility indicators, corresponding contextual questions in active monitoring, and PANSS negative symptom scores. We define a moderate statistically significant correlation (ie, Spearman rho>0.35) as the validity threshold.

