### Statistical Analysis Plan

All quantitative analyses will be performed using R (version 4.0.5) [66]. Feasibility data and safety data including (1) recruitment and retention data, (2) app usage data, (3) completeness of study measures, and (4) the number and nature of adverse events will be analyzed using appropriate descriptive statistics (mean and standard deviations for continuous data; counts and percentages for categorical data). Logistic regression and linear regression analyses will be used to explore sociodemographic and clinical characteristics and device attributes as predictors of feasibility (eg, dropouts, app usage).

The active monitoring will generate 3 levels of data, with the data entered for each “beep” as level 1, nested within the level 2 “day” level, which is nested within the level 3 subject level. Because the PANSS and CDSS measure participants’ symptoms for the past week, and to minimize the impact of missing data, the subject level mean score of the first week will be used to calculate the association between active monitoring items score and relevant symptom domain scores of the PANSS and CDSS at the week 1 follow-up assessment to evaluate validity. The significance level for the study will be set to .05. Cronbach alpha will be used to calculate the internal consistency reliability of the sets of the items of active monitoring. To account for the nested structure of the data, multilevel models will be used to explore the instability of the different constructs across time and patterns of missing data.

The GPS mobility indicators will be extracted from passive monitoring data. The convergent validity of passive monitoring will be calculated by the correlation between GPS mobility indicators and the PANSS negative symptom score. Discriminant validity of passive monitoring will be demonstrated by low correlation between GPS mobility indicators and positive symptoms measured by PANSS.

Qualitative data will be transcribed verbatim in Chinese and then translated to English by the principal researcher. A framework analysis approach will be used based on the protocol by Braun and Clarke [67], which consists of the following 6 phases of thematic analysis: familiarization, transcription, generating initial codes, searching for themes, reviewing themes, and defining and deciding on meaningful themes. Nvivo software (version 12) [68] will be used to manage the qualitative data.

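### The validity correlations pool diagnosed and clinical-high-risk participants, so a severity gap between the groups can inflate rho in a study that concludes for people with psychosis

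*Protocol article*

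**What the plan says.** Two populations are eligible. In the protocol article, Eligibility Criteria (Textbox 1), the diagnostic criterion is met by people who have a schizophrenia-spectrum diagnosis "or met the criteria for being at clinically high risk for developing psychosis according to the Structured Interview for Prodromal Syndromes (SIPS"). No cap on the second group is stated.

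The target population is described more narrowly. Study Objectives sets out to evaluate "a symptom self-monitoring smartphone app (YouXin) for people with psychosis in China", and Study Design reports the sample as "We recruited 40 people with psychosis at a tertiary-level psychiatric hospital in Beijing, China".

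The validity analysis is fixed in two places:
- Validity: "The validity of active monitoring items will be assessed against relevant clinical assessments (ie, PANSS and CDSS) using Spearman correlation", with the decision rule "We define a moderate statistically significant correlation (ie, Spearman rho>0.35) as the validity threshold".
- Statistical Analysis Plan: "the subject level mean score of the first week will be used to calculate the association between active monitoring items score" and the relevant PANSS and CDSS domain scores at the week-1 assessment. Also, "The significance level for the study will be set to .05".

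Neither section mentions diagnostic group. The same holds for the GPS correlations with PANSS negative and positive symptoms.

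**The concern.** Each participant contributes one app mean and one clinical score per domain, so each rho is purely between persons. Over two populations, such a correlation has two sources: how well the app ranks people inside each group, and how far apart the groups lie on both measures. The second is known-groups separation, which the diagnostic interviews already provide. A tool meant to monitor symptoms in people with psychosis needs the first.

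The threshold is a pass/fail rule and the conclusion is drawn for people with psychosis. A group contrast could therefore lift a weak association in the diagnosed group over 0.35. For the GPS indicators, a shared gap could strengthen the correlations with both negative and positive symptoms. That would flatter convergent validity and, at the same time, spoil the low correlation wanted for discriminant validity.

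**Working it through.** **Inputs from the protocol article.** n = 40 (Study Design); Spearman correlation and threshold 0.35 (Validity); alpha 0.05 (Statistical Analysis Plan), taken as two-sided because the side is not stated.

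**Assumed inputs, not in the documents.** p, the high-risk share; d, the gap between groups in within-group SDs, equal on app score and clinical scale unless stated; normal scores with equal SD in both groups; no association within either group unless stated.

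**1. Which part of the rule binds at n = 40.** The protocol derives no sample size from the threshold, so there is no calculation to reproduce. The critical rho is t/√(n − 2 + t²). With t = 2.024 on 38 df, 2.024/√(38 + 4.10) = 0.312. This is below 0.35, so the 0.35 condition binds.

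**2. Pooled rho from the group gap alone.** Population Spearman = 12p(1 − p)[Φ(d/√2) − 0.5]².
- 10/40, d = 1: 12 × 0.25 × 0.75 × (0.760 − 0.5)² = 2.25 × 0.0677 = 0.15.
- 20/40, d = 1: 3 × 0.0677 = 0.20.
- 10/40, d = 1.77: 2.25 × (0.895 − 0.5)² = 0.35.
- 20/40, d = 1.42: 3 × (0.842 − 0.5)² = 0.35.

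**3. Gap needed to reach 0.35, and the ceiling.** Under complete separation Φ tends to 1, so the ceiling is 3p(1 − p).

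| High-risk of 40 | Ceiling | Gap for rho = 0.35 (SD, both measures) |
|---|---|---|
| 4 | 0.27 | not reachable |
| 5 | 0.328 | not reachable |
| 6 | 0.382 | 2.86 |
| 8 | 0.48 | 2.06 |
| 10 | 0.562 | 1.77 |
| 12 | 0.63 | 1.61 |
| 16 | 0.72 | 1.46 |
| 20 | 0.75 | 1.42 |

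**4. Unequal gaps.** The squared bracket becomes the product of two brackets, one for each measure. With 2 SD on one and 1 SD on the other, rho is 0.25 (10/40) or 0.33 (20/40), both below the threshold.

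**5. Chance that an observed rho exceeds 0.35 at n = 40** (simulation, 20,000 runs, no within-group association). Without a mixture it is 1.2%.

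| High-risk of 40 | d = 1 | d = 1.5 | d = 2 |
|---|---|---|---|
| 4 | 4% | 8% | 13% |
| 10 | 10% | 33% | 67% |
| 20 | 17% | 60% | 95% |

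**6. Weak rather than absent association.** With a within-group Spearman of 0.20, the pooled value reaches 0.35 at a gap of 1.14 SD (10/40). The chance of an observed rho above 0.35 rises from 16% unmixed to about 42% at 10/40 and 1 SD.

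**The case against.** The strongest reply is that the concern rests on silence. Only an article is shown, and subgroup or adjusted correlations are often left to a fuller plan. Nothing in the text says that diagnostic group will be ignored; pooling is inferred from the absence of any split. This limits how firmly the point can be put. It does not remove it, because the article itself fixes the statistic, the unit of analysis and the pass mark, and itself describes a mixed eligible population as people with psychosis.

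A reader might infer that validity hangs on one pooled correlation that could pass with no validity at all in psychosis. The documents do not support that reading:
- There are several correlations, by PANSS and CDSS domain, and the artefact arises only in domains where the groups differ. The documents give no reason to expect a gap on the CDSS mood items.
- Reaching 0.35 from the gap alone takes about 6 or more high-risk participants of 40 and a gap of roughly 1.4 to 2.9 SD on both measures. Neither figure is reported.
- Excluding clinically unstable people may narrow the gap.
- No association inside either group, alongside wide separation between them, is a limiting case.

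Two further objections stand in part. The criteria were deliberately broad, although the breadth is justified for service users with psychosis, which does not describe the high-risk group. High-risk status is also related to severity, so adjusting for it may remove genuine between-person variance, and a diagnosed-only analysis narrows the range and reduces n. These are reasons to keep the pooled rho in the report. They do not justify showing it alone.

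**Conclusion.** The concern holds in limited form. Eligibility is wider than the stated population, and the validity correlations carry no stated split or term for diagnostic group. A severity gap can therefore inflate the pooled rho in the affected domains. Under the assumptions above, a 1 SD gap on both measures with no within-group association gives a population rho of about 0.15 (10/40) to 0.20 (20/40). That falls short of 0.35 in expectation, but it is enough to help a weak association across the line. The gap alone reaches 0.35 only at large assumed gaps, and never in expectation with 5/40 or fewer at high risk. The documents do not show that this happened or that it is likely. They leave a pooled pass unable to separate tracking of severity within psychosis from a difference between the two groups.

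**What to change.** 1. Report the number of diagnosed and high-risk participants.
2. Beside each pooled rho, give the rho within the diagnosed group with its confidence interval, and a partial Spearman rho adjusted for diagnostic group. Do the same for the exploratory GPS correlations with negative and positive symptoms.
3. Claim validity for people with psychosis only where the within-psychosis estimate is consistent with the pooled result, and set down before analysis what will count as consistent. Otherwise state the conclusion for the mixed psychosis and high-risk sample.
4. Reconcile the description of the sample in Study Design with the inclusion criteria in Textbox 1.

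The cost is small. Diagnostic group is established at eligibility, and the analyses are still described as planned, so no new data are needed. The downside is precision: recruitment is closed, and with 30 diagnosed participants the critical rho is 2.048/√(28 + 4.19) = 0.361, so significance becomes a stricter condition than 0.35. Because adjustment may also take out some real severity variance, the pooled rho should stay in the report.
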